### Outcome measures

All study variables will be assessed under standardized conditions at each evaluation point in order to minimize measurement variability.

#### Primary outcome.

The primary outcome of this trial will be the functional capacity, assessed using the Six-Minute Walk Test (6MWT). This submaximal exercise test will be administered following standardized procedures as established by the American Thoracic Society (ATS) and the European Respiratory Society (ERS) [34,35]. The 6MWT quantifies the maximum distance (in meters) that a person can walk in six minutes along a flat, 30-meter corridor, providing an objective measure of submaximal aerobic endurance, cardiorespiratory fitness, and overall physical function [35].

The 6MWT is considered a valid and reliable outcome measure in patients undergoing CRC surgery, as it reflects functional recovery trajectories and physical performance throughout the perioperative period [35,36]. By capturing the integrative physiological response of the cardiovascular, respiratory, and musculoskeletal systems, the test offers a comprehensive indicator of physical capacity and is sensitive to clinically meaningful changes over time [37,38].

#### Secondary outcomes.

Secondary outcomes are prespecified as either key supportive secondary outcomes, including muscle strength, body composition, pulmonary function, and health-related quality of life, or as exploratory and implementation-focused outcomes, including physical activity, sleep quality, psychosocial variables, treatment expectancy, usability, satisfaction, and adherence. This distinction is intended to enhance interpretability and to clarify that not all secondary endpoints are meant to support confirmatory inference to the same extent.

#### Body composition.

Body composition will be assessed using bioelectrical impedance analysis (BIA) with the Tanita BC-601 InnerScan®V (Japan) device. This validated, non-invasive method provides estimates of visceral fat percentage, total body weight, body fat percentage, skeletal muscle mass, and total body water [39,40]. BIA is widely used in both clinical and research settings because of its reproducibility, ease of use, and ability to track changes in body composition over time [39,41]. Because BIA-derived estimates may be influenced by hydration status and perioperative inflammatory changes, these measures will be interpreted cautiously and in conjunction with anthropometric variables and ultrasound assessment of the rectus femoris muscle rather than as stand-alone indicators of true changes in muscle or fat mass. Whenever feasible, BIA assessments will be scheduled at the same time of day and under consistent pre-assessment conditions across time points in order to reduce short-term measurement variability. These parameters nevertheless provide useful complementary information on metabolic status, body composition, and exercise tolerance in patients undergoing CRC treatment.

In addition to BIA, waist and hip circumference will be measured according to a standardized anthropometric protocol to assess central adiposity. These anthropometric indices are clinically relevant because they are strongly associated with metabolic dysfunction, systemic inflammation and cancer-related prognostic factors [42]. In the context of CRC rehabilitation, increased visceral adiposity and low muscle mass (i.e., sarcopenia) have been associated with poorer functional outcomes, higher rates of postoperative complications, and delayed recovery [43,44]. These anthropometric measures will therefore be interpreted alongside BIA and ultrasound findings to support a more comprehensive evaluation of perioperative body-composition changes.

#### Ultrasound assessment of the rectus femoris muscle.

Ultrasound imaging of the rectus femoris muscle will be used to assess skeletal muscle morphology and to monitor changes in muscle mass as a surrogate marker for nutritional status and sarcopenia. This non-invasive, bedside technique has shown high validity and reliability in both oncology and surgical populations and is widely used to detect early muscle wasting in patients undergoing cancer treatment or major surgery [45,46].

The assessments will be performed using a high-frequency (7–12 MHz) linear transducer, with the participant in a relaxed supine position. The transducer will be placed perpendicularly at the lower third (distal third) of the distance between the anterior superior iliac spine (ASIS) and the superior border of the patella on the dominant leg, following standardized anatomical landmarks to ensure reproducibility and accuracy across different time points [47].

The main parameters recorded will include muscle thickness, cross-sectional area (CSA) and echogenicity, the latter being analyzed using grayscale histogram analysis as a marker of muscle quality and intramuscular adiposity. This method allows the monitoring of musculoskeletal adaptations during the perioperative period and the response to therapeutic exercise and nutritional interventions [48].

In patients with CCR, reduced muscle thickness and increased echogenicity of the rectus femoris have been independently associated with higher postoperative complication rates, longer hospital stays, and impaired clinical outcomes [49]. Therefore, serial ultrasound assessments provide valuable complementary data to conventional anthropometric and functional measurements, supporting a comprehensive and dynamic evaluation of the patient status throughout the rehabilitation process.

#### Muscle strength.

Muscle strength will be assessed using two validated functional tests: the Handgrip Strength Test (HGS) for upper limb strength, and the Five-Repetition Sit-to-Stand Test (5R-STS) for lower limb function. Both measures are widely used in oncologic rehabilitation as indicators of neuromuscular performance, physical independence, and postoperative recovery potential [50,51].

Upper limb strength will be evaluated using a hydraulic hand-held dynamometer (Jamar® Hand Dynamometer, Sammons Preston Rolyan, Bolingbrook, IL, USA) following standardized testing procedures [52]. The participants will be seated in a shoulder neutral position, the elbow flexed at 90°, and the wrist in a neutral posture. Each participant will perform three maximal voluntary contractions with each hand, holding the grip for three seconds. The highest value (in kilograms) will be recorded for analysis. Handgrip strength is considered a robust surrogate marker for sarcopenia and nutritional status and is predictive of postoperative complications and overall prognosis in CRC patients [53].

Lower limb strength will be assessed using the 5R-STS, in which participants are instructed to stand up and return from a sitting position five times as quickly as possible, with their arms crossed over the chest to avoid upper limb compensation. The total time (in seconds) will be recorded using a standardized chair height (43–47 cm) to ensure consistency. This test reflects the functional mobility and the lower-extremity muscle power, and is strongly associated with fall risk, frailty, and recovery of autonomy after surgery [51,54].

#### Pulmonary function (spirometry).

Pulmonary function will be evaluated using standardized spirometry to assess changes in respiratory capacity associated with the telerehabilitation intervention. The two primary parameters to be measured will be: 1) Forced Vital Capacity (FVC): the maximum volume of air forcibly exhaled following a full inhalation and 2) Forced Expiratory Volume in 1 second (FEV₁): the volume of air exhaled during the first second of the forced expiratory maneuver [55].

The spirometry measurements will be conducted using a calibrated digital spirometer, following the technical standards established by the ERS and the ATS [56]. Each participant will perform a minimum of three acceptable and reproducible forced expiratory maneuvers while seated, and the highest consistent value will be retained for analysis. The results will be expressed both in absolute terms (liters) and as a percentage of the predicted values, adjusted for age, gender, height, and body weight [56].

In the perioperative management of CRC, a reduction in lung function is frequently observed, which is associated with a higher rate of postoperative pulmonary complications and delayed mobilization. Specifically, decreased preoperative FVC has been identified as an independent predictor of pulmonary complications such as pneumonia after colorectal cancer surgery [57]. Similarly, a large cohort study in high-risk abdominal surgery patients demonstrated that each 1% increase in preoperative FVC was associated with a 2% reduction in the risk of postoperative pulmonary complications [58]. Spirometry provides a clinically meaningful and objective indicator of respiratory performance and preoperative risk stratification [59].

In this study, spirometry assessments will be performed at several time points to compare the development of respiratory function between the groups. This will help to determine whether participation in the telerehabilitation program, particularly the structured respiratory training component, leads to better maintenance or improvement of lung capacity compared to standard leaflet-based rehabilitation.

#### Physical activity level (IPAQ-SF).

Self-reported level of physical activity will be assessed using the International Physical Activity Questionnaire – Short Form (IPAQ-SF). This validated tool is widely used in clinical and epidemiologic research to quantify habitual physical activity in adults and to monitor changes in response to health interventions [60,61].

The IPAQ-SF consists of seven items that measure the frequency and duration (minutes per day and days per week) of physical activity performed in the past seven days across three intensity domains: vigorous activity, moderate activity and walking, and time spent sitting. The answers will be used to calculate total physical activity in minutes per week (Metabolic Equivalent Task, MET-min/week) and allow categorization into low, moderate or high physical activity according to the IPAQ scoring protocol [60].

This questionnaire has shown acceptable reliability and validity for the assessment of physical activity levels in cancer survivors and perioperative patients [62,63]. In the context of CRC rehabilitation, physical activity monitoring is critical to understanding behavioral adaptations, adherence to exercise recommendations, and their potential associations with clinical recovery, functional outcomes, and QoL.

The IPAQ-SF will be administered at each of the five time points (T1–T5), allowing longitudinal analysis of changes in physical activity levels during the intervention and follow-up periods.

#### Sleep quality (pittsburgh sleep quality index – PSQI).

Sleep quality will be assessed using the Pittsburgh Sleep Quality Index (PSQI), a widely validated self-report questionnaire to measure sleep disturbances and habitual sleep patterns in the past month [64]. The PSQI is considered the gold standard for assessing sleep in clinical and oncology patients’ populations due to its reliability, multidimensional structure, and sensitivity to change [65,66].

The questionnaire consists of 19 items, which are divided into seven components: Subjective sleep quality, sleep latency, sleep duration, habitual sleep efficiency, sleep disturbances, use of sleep medication, daytime sleep disturbances.

Each component is scored on a scale from 0–3, resulting in a global score ranging from 0 to 21, with higher scores indicating poorer sleep quality. A total PSQI score of >5 is generally used as a cut-off point for clinically significant sleep disturbance [64].

In CRC patients, poor sleep quality has been associated with increased fatigue, mood disturbances, impaired immune function and lower health-related quality of life, particularly during the perioperative and adjuvant treatment phases [67].

Assessment of sleep patterns throughout the rehabilitation process will provide important insights into the psychosomatic impact of telerehabilitation and help to identify potential areas for supportive care interventions. The PSQI will be administered at all five evaluation time points (T1–T5) to monitor changes in sleep quality over time and compare results between groups.

#### Psychosocial factors.

Psychological response to cancer and emotional distress will be assessed using two validated instruments: the Mental Adjustment to Cancer questionnaire (MAC) and the Hospital Anxiety and Depression Scale (HADS).

The MAC questionnaire evaluates patients’ cognitive-behavioral coping styles in the context of cancer. It distinguishes between adaptive (positive adjustment) and maladaptive (negative adjustment) responses. Higher scores on the positive dimensions, such as fighting spirit and positive orientation to the illness, reflect active, goal-oriented coping strategies that have been associated with greater psychological resilience and improved treatment adherence [68,69]. Conversely, elevated scores in the negative domains, such as helpless–hopelessness, anxious preoccupation, or fatalism, indicate passive or avoidant coping mechanisms, which are typically associated with emotional distress, reduced QoL, and poorer clinical prognosis [70].

The HADS, a screening tool widely used in oncology for detecting clinically relevant symptoms of anxiety and depression, will be used in the study to assess emotional symptoms. The scale consists of 14 items, equally divided into two subscales: HADS-Anxiety (HADS-A) and HADS-Depression (HADS-D). Each item is rated from 0 to 3, yielding subscale scores ranging from 0 to 21. In clinical practice, the following cut-off thresholds are commonly used: 0–7 (normal), 8–10 (borderline or mild symptoms), and ≥11 (probable clinical case) [71,72].

In CRC populations, elevated HADS scores have been consistently associated with increased psychological burden, diminished QoL, and reduced engagement with treatment regimens. Therefore, the interpretation of MAC and HADS scores will be placed in the context of each patient’s overall clinical profile. In the case of high-risk scores, a comprehensive psychosocial evaluation and referral to mental health or psycho-oncology services when indicated [70].

#### Quality of life EuroQol 5D.

Health-related quality of life (HRQoL) will be assessed using the EuroQol-5D (EQ-5D) questionnaire, a validated and widely used self-administered instrument to measure general health status and patient-reported outcomes [73,74]. The EQ-5D captures key domains of physical and psychosocial functioning and is particularly valuable for monitoring changes in health-related quality of life during cancer treatment and rehabilitation [75,76].

The instrument comprises two components: 1) The EQ-5D descriptive system, which evaluates five health dimensions: mobility, self-care, usual activities, pain/discomfort, and anxiety/depression. Each dimension is rated on five levels in the EQ-5D-5L version (ranging from “no problems” to “extreme problems”). The combination of these ratings produces a five-digit health profile, which can be converted into a utility index (EQ-5D index) using a country-specific assessment algorithm. This index ranges from 0.000 (equivalent to death) to 1.000 (full health) and may also include negative values, representing health states perceived as worse than death [74]. 2) The EQ Visual Analogue Scale (EQ-VAS), which captures the participant’s self-perceived overall health status. Participants indicate their current state of health on a vertical scale ranging from 0 (worst imaginable health state) to 100 (best imaginable health state) [73].

In the context of oncological rehabilitation, especially for patients undergoing CRC surgery, the EQ-5D is a widely used tool to assess the treatment burden, the course of recovery and the impact of supportive interventions on physical, emotional and social well-being [75,77,78].

#### Treatment expectancy (Stanford Expectations of Treatment Scale – SETS).

Treatment expectancy will be assessed using the Stanford Expectations of Treatment Scale (SETS), a validated self-report instrument designed to measure patients’ beliefs and expectations regarding the effectiveness and potential benefits of a therapeutic intervention [79]. This construct has been shown to influence treatment adherence, engagement, and clinical outcomes, particularly in the context of behavioral and rehabilitative interventions [80].

The SETS consists of 6 items, each of which is rated on a 7-point Likert scale ranging from 1 (“strongly disagree”) to 7 (“strongly agree”). The scale captures two dimensions of expectancy: (1) outcome expectancy, defined as the belief that the treatment will be beneficial, and (2) process expectancy, defined as the belief that the treatment will be delivered competently and professionally [79].

The item scores are summed to produce a global expectancy score, with higher scores indicating more positive treatment expectations. The SETS has demonstrated good psychometric properties, including internal consistency and predictive validity, in populations undergoing various physical and psychological interventions [79,80].

In the context of prehabilitation and postoperative rehabilitation for CCR, patient expectations may play a critical role in motivation, engagement with home-based programs, and perceived benefit of telerehabilitation. By including the SETS, this study will explore the potential moderating effect of expectancy on treatment response [79].

The SETS will be administered at baseline (T1) to capture initial expectations before the intervention and at post-intervention (T4) to investigate possible changes in perception over time.

#### Telehealth usability (Telehealth Usability Questionnaire – TUQ).

The usability and user experience of the telerehabilitation platform will be assessed using the Telehealth Usability Questionnaire (TUQ), a validated instrument specifically designed to evaluate patients’ perceptions of telehealth systems across multiple domains [81]. The TUQ provides a comprehensive assessment of the practicality, satisfaction and perceived value of remote healthcare delivery tools, and has been validated in a variety of clinical and technological contexts, including applications in cancer rehabilitation and chronic disease management [82,83].

The TUQ consists of 21 items, each of which is rated on a 7-point Likert scale (1 = strongly disagree to 7 = strongly agree), covering six core dimensions: Usefulness, ease of use and learnability, interface quality, interaction quality, reliability, satisfaction and future use [81].

A total and subscale score will be calculated from the item responses, with higher values indicating better usability and user satisfaction. The questionnaire will be administered exclusively to the participants of the IG (telerehabilitation) at the end of the postoperative rehabilitation phase (T4), to evaluate their experience with the HEFORA platform.

Understanding the usability of digital health tools is essential for interpreting adherence and engagement in the telerehabilitation context. The TUQ will provide key insights into the acceptability, accessibility, and perceived value of the asynchronous platform used in this study, which can serve as a basis for future implementation and scalability strategies.

#### Patient satisfaction.

Patient satisfaction with the rehabilitation program will be evaluated using an ad hoc satisfaction survey. This approach has been widely employed in oncology rehabilitation and digital health studies, as patient-reported satisfaction is a key determinant of intervention feasibility, adherence, and long-term sustainability [84,85]. The instrument aims to assess the participants’ subjective perception of the intervention received, whether through the telerehabilitation platform or the standard leaflet-based approach, focusing on the quality of the content, the delivery modality and the overall user experience.

The survey includes two core questions that apply to all participants, which evaluate: 1) Satisfaction with the overall exercise program and 2) Satisfaction with the attention and support received during the intervention.

In addition, participants in the IG will rate: 1) The HEFORA platform (accessibility and ease of use); 2) The exercise video materials; 3) The clarity of exercise instructions and 4) The educational video content. Participants in the CG will provide feedback on the educational leaflet.

Each item will be scored on a 5-point Likert scale ranging from 0 (“very dissatisfied”) to 4 (“very satisfied”). The Satisfaction Survey will be administered at two time points: T2 (post-prehabilitation): To assess early impressions and engagement following the prehabilitation phase, immediately before surgery. T4 (post-rehabilitation): to evaluate overall satisfaction after completion of the full intervention protocol (4 weeks postoperatively).

Measuring patient satisfaction at both stages of the intervention will provide important insights into adherence and participant engagement, factors that are critical to the success and future implementation of telerehabilitation in oncologic surgical pathways [86,87].

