### Procedure

The recruitment process will be carried out in the Department of General and Digestive Surgery of the Royo Villanova Hospital (Zaragoza, Spain) under the coordination of the Head of Department. During the first preoperative consultation, eligible candidates will receive a comprehensive information sheet detailing the study objectives, procedures, potential risks and benefits, and contact details of the principal investigator for further questions.

Patients who express an interest in participating will be screened by a trained researcher to ensure that they meet the inclusion and exclusion criteria. Once enrolled, participants will sign the informed consent form and complete a baseline evaluation (T1: pre-prehabilitation) conducted by a physiotherapist blinded to group allocation. This assessment will include standardized questionnaires and physical performance tests. Questionnaires will be administered in a standardized manner in both groups, and the physiotherapist conducting the assessment will be available only to clarify item wording and ensure consistent understanding, without influencing participants’ responses. Each session will last approximately 45 minutes and will be performed in the hospital under standardized conditions to enhance the measurement reliability and minimize external variability.

After the initial assessment, participants will be randomized into one of two study groups: (1) the IG, which will receive the structured asynchronous telerehabilitation program; or (2) the CG, which will receive the same multimodal physiotherapy content through a booklet-based usual-care program.

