**Fig 2 pone.0333649.g002:**
[figure not shown]
Schedule of enrollment, interventions, and assessments.

All participants will be instructed to maintain a daily exercise log, either digital or paper-based, to document adherence. Adherence will be recorded using a structured adherence diary indicating whether each prescribed exercise session was completed fully, partially, with modifications, or not completed, together with post-session fatigue rated on a 0–10 numerical rating scale and the occurrence of any adverse effects. In the IG, exercise progression and safety will be monitored asynchronously through the HEFORA platform. In the CG, follow-up will be conducted through the booklet, routine clinical reviews, scheduled assessments, and verification of the paper-based adherence diary during those visits by a physiotherapist not involved in blinded outcome assessment. Reminders and adaptive exercise progression will also be provided in the CG, but only within the context of face-to-face clinical follow-up rather than through asynchronous digital monitoring.

Study outcomes will be evaluated at five key time points: Time 1 (T1): pre-prehabilitation (baseline assessment); Time 2 (T2): post-prehabilitation (pre-surgery, the day before surgery); Time 3 (T3): pre-rehabilitation (post-surgery-day 21, after suture removal); Time 4 (T4): post-rehabilitation (day 50, after completion of the rehabilitation phase) and Time 5 (T5): follow-up (three months after T4 by telephone assessment).

Assessments at T1, T2, T3, and T4 will be conducted in person by the same physiotherapist, who will remain blinded to group allocation throughout the study. All evaluations will follow a standardized protocol to ensure consistency across time points. Performance-based assessments will be administered using identical instructions and procedures across groups and time points in order to reduce the risk of differential assessment bias. The final follow-up (T5) will be conducted remotely using a structured telephone interview to assess long-term psychosocial well-being and health-related quality of life.

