## Discussion

The main objective of this randomized controlled trial is to evaluate the effectiveness of an asynchronous telerehabilitation program delivered through the HEFORA digital platform, across both the prehabilitation and postoperative recovery phases, compared with a booklet-based usual-care program reflecting the perioperative pathway routinely available in the study setting before trial implementation. The study responds to the growing clinical need to mitigate perioperative deterioration while addressing the logistical and geographic barriers that often limit access to center-based rehabilitation programs. By integrating multimodal components into a home-based, digitally supported protocol, this trial proposes a patient-centered strategy that may improve continuity of care during one of the most vulnerable phases of the oncologic trajectory.

The 6MWT was selected as the primary outcome because it is a valid and clinically meaningful measure of functional capacity in surgical and oncology populations. Its clinical relevance is supported by consistent associations between improvements exceeding the minimal clinically important difference (MCID) and reduced postoperative morbidity and shorter hospital stays [5,91,92]. By assessing this variable at four perioperative time points, this study acknowledges the dynamic and non-linear functional trajectories described in patients with CRC [92]. At the same time, performance in the 6MWT may reflect not only physiological adaptation but also motivation, engagement, familiarization, and confidence fostered by ongoing support. Accordingly, any between-group differences in walking performance should be interpreted as potentially arising from a combination of physiological and behavioral mechanisms. To reduce the risk of differential assessment bias, performance-based outcomes will be administered by a blinded assessor using the same standardized instructions and procedures in both groups at each time point. This interpretation is further strengthened by the inclusion of additional objective outcomes, including muscle strength, spirometry, body composition, and ultrasound-based muscle assessment.

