A key limitation of this trial is the brief two-week prehabilitation phase, which is determined by the usual interval between diagnosis and surgery in the study setting. Although this timeframe is clinically realistic, it may limit the extent of physiological gains achievable before surgery, particularly in relation to muscle strength and functional reserve. Accordingly, the prehabilitation component should be interpreted primarily as a pragmatic optimization window embedded within routine surgical care rather than as a stand-alone training period expected to produce substantial physiological adaptations in all participants. Additional limitations arise from the pragmatic comparator design. Both groups receive the same multimodal physiotherapy content, and both include physiotherapist-led follow-up; therefore, any between-group differences are more likely to reflect differences in delivery, monitoring, progression, reminders, and continuity of support than differences in exercise content itself. Because the telerehabilitation group receives more continuous platform-supported monitoring between visits, this design may introduce cointervention imbalance, performance bias, and some uncertainty in attributing observed effects specifically to the digital component in isolation. In addition, several secondary outcomes are derived from self-reported questionnaires and may therefore be influenced by expectancy effects, engagement bias, and novelty-related responses associated with digital delivery. To reduce misunderstanding during questionnaire completion, these instruments will be administered in a standardized manner in both groups, and the physiotherapist will be available only to clarify item wording and ensure consistent understanding rather than to guide responses. While these measures are necessary to assess psychosocial, behavioral, usability, and satisfaction-related domains that are not fully captured by objective performance-based assessments, their findings should be interpreted cautiously and in the context of the objective assessor-administered outcomes. Similarly, BIA-derived estimates may be influenced by perioperative shifts in hydration and inflammation and should therefore be interpreted alongside anthropometric and ultrasound-based assessments rather than as direct evidence of true changes in muscle or fat mass. Whenever feasible, BIA assessments will also be scheduled at the same time of day to reduce short-term variability related to fluid balance and daily fluctuations. Finally, this is a single-center study with a relatively small sample drawn from a selected population of patients undergoing elective colorectal cancer surgery. In addition, the exclusion of frail patients and adults older than 80 years may limit the generalizability of the findings to more vulnerable perioperative populations. Future multicenter studies including broader eligibility criteria and longer or more individualized prehabilitation periods will be necessary to establish the external validity of this intervention.

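### The blinded assessor who runs every 6MWT is also the person available to clarify questionnaires with arm-specific items at T2, so allocation may be learned before the T3 and T4 walks, with no stated safeguard

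*Protocol article*

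**What the plan says.** **Who assesses.** The Procedure section (text after Fig 2) says: "Assessments at T1, T2, T3, and T4 will be conducted in person by the same physiotherapist, who will remain blinded to group allocation". The Discussion confirms that the 6MWT is measured at four of the five time points ("By assessing this variable at four perioperative time points"). T5 is by telephone, so the walks are those at T1 to T4.

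**Who attends the questionnaires.** The Procedure section, describing the baseline visit, says that "the physiotherapist conducting the assessment will be available only to clarify item wording and ensure consistent understanding". The limitations paragraph of the Discussion repeats the arrangement for the self-report instruments in general: "the physiotherapist will be available only to clarify item wording and ensure consistent understanding rather than to guide responses". The next sentence counts usability and satisfaction among the domains that these instruments cover.

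**What the forms contain.** Under Patient satisfaction, two items are common to both arms. Then: "In addition, participants in the IG will rate: 1) The HEFORA platform (accessibility and ease of use"), followed by the exercise videos, the clarity of instructions and the educational videos. Control participants comment on the leaflet instead. On timing: "The Satisfaction Survey will be administered at two time points: T2 (post-prehabilitation") and T4. Under Telehealth usability, for the Telehealth Usability Questionnaire (TUQ): "The questionnaire will be administered exclusively to the participants of the IG (telerehabilitation"), at T4.

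**What is kept apart.** Allocation and blinding bars the researcher who delivers the intervention from all assessment. The Procedure section gives verification of the control group's paper diary to a physiotherapist outside the blinded assessments. No such separation is stated for the satisfaction survey or the TUQ, and no order of tests within a visit is given.

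**The concern.** A form that asks about HEFORA or about the leaflet identifies the arm to anyone who sees it or is asked to explain an item on it. If the blinded assessor is that person at T2, the arm can be known from then on, because the same assessor returns for T3 and T4.

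The trial leans heavily on this blinding. Neither participants nor treating staff are blinded, so the assessor's is the only blinding there is. The Discussion accepts that walking distance may reflect motivation, engagement and confidence as well as physiology. It names the blinded assessor, with standardized instructions, as the protection against assessing the two arms differently. It also asks readers to weigh the self-report results against the outcomes that this assessor measures. A loss of blinding would therefore touch the primary outcome and also the strength, spirometry and ultrasound measures. It could not be repaired in the analysis.

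**Working it through.** The plan states no figure on this point, so the check is mainly a reading of the sections together.

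**Step 1: is the blinded assessor the person at the questionnaires?** Procedure has one blinded physiotherapist conduct T1 to T4, and makes the assessing physiotherapist the one who clarifies items. The clarifying sentence stands in the paragraph on T1, which precedes randomization, so alone it could be confined to baseline. The Discussion prevents that: it applies the arrangement to instruments that include satisfaction and usability measures. The satisfaction survey is given only at T2 and T4, and the TUQ only at T4. The arrangement must therefore reach visits after randomization.

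**Step 2: which walks follow a possible disclosure?**

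| Visit | 6MWT | Form that differs by arm | Walk exposed? |
|---|---|---|---|
| T1 | yes | none (before randomization) | no |
| T2 | yes | satisfaction survey | only if the survey comes first |
| T3 | yes | none | yes, through T2 |
| T4 | yes | satisfaction survey, TUQ | yes, through T2; the T4 forms add to this only if given before the walk |
| T5 | no | none stated | not applicable |

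The T2 survey alone carries the argument. Two of the three post-baseline walks follow it whatever the order within a visit.

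**Step 3: how much could it matter?** The documents give no figure for assessor bias, so this is an illustration on assumed values.

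- Inputs from Sample size calculation: SD 80 m, target difference 60 m, two-sided alpha 0.05, 28 per group enrolled, 23 per group before the dropout allowance.
- Assumption: a bias of b metres shifts the between-group difference at one time point, and there is no true effect.
- Standard error: SE = 80 × √(2/n). For n = 28 this is 80 × √(2/28) = 21.4 m; for n = 23 it is 80 × √(2/23) = 23.6 m.
- Two-sided rejection rate: 1 − Φ(1.96 − b/SE) + Φ(−1.96 − b/SE).
- Worked case, b = 10 and n = 28: b/SE = 10/21.4 = 0.47, and the rate is about 0.068 + 0.008 = 7.5%.

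| Assumed bias b | Share of 60 m | Type I error, n = 28 | Type I error, n = 23 |
|---|---|---|---|
| 5 m | 8% | 5.6% | 5.5% |
| 10 m | 17% | 7.5% | 7.1% |
| 15 m | 25% | 10.8% | 9.7% |
| 20 m | 33% | 15.5% | 13.6% |

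Small biases do little harm; biases of a quarter to a third of the target difference raise the error to between about two and three times its nominal level. Nothing in the documents says where in this range, if anywhere, the trial would fall.

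**The case against.** The strongest reply is that disclosure is nowhere documented. The Patient satisfaction and Telehealth usability sections name no administrator. No sentence says that the assessor hands out, reads or collects these forms. The Discussion says only the physiotherapist, and a second physiotherapist is present at the scheduled visits to verify diaries. A journal article also often leaves form handling to working instructions. Finally, the walk follows published standards with the same instructions in both arms, which narrows the room for uneven encouragement.

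Much of this stands. A reader might infer that allocation is revealed for every participant at T2. The text supports only exposure to that risk, and all participants is a ceiling, not an estimate. A reader might also see a second leak in the control group's paper diaries, but Procedure already gives their verification to someone outside the blinded assessments. The T4 forms cannot be counted against the T4 walk unless they precede it, and T4 is the last walk.

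The reply does not remove the conflict. The article does more than stay silent: it says who clarifies questionnaire items and says that this person stays blinded throughout. It separates other staff and the diary check from blinded assessment, but not these two forms. Standardized instructions limit bias but do not replace blinding in an effort-dependent test.

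**Conclusion.** The point holds as an unguarded risk of unblinding. Taken together, the Procedure section, the Discussion and the satisfaction-survey description place the blinded assessor where allocation can be learned at T2, before the T3 and T4 walks, and no safeguard is stated. The T2 walk, and any added effect of the T4 forms on the T4 walk, depend on an order within the visit that is not given.

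This rests on reading the Discussion's physiotherapist as the assessing physiotherapist named in Procedure. That is the natural reading but not the only possible one. The documents do not show that blinding has been broken, nor that 6MWT results are biased by any particular amount. The metres and error rates in the illustration are assumptions. The matter is a cheap improvement worth making, because it protects the trial's only blinding.

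**What to change.** State in the protocol that the satisfaction survey and the TUQ are handed out, clarified and collected by the physiotherapist outside the blinded assessments who already verifies the control diaries. This should be done out of the blinded assessor's sight and after that visit's performance tests, with completed forms withheld from the assessor. Changing the order alone is not enough: a survey given after the T2 walk but handled by the assessor would still reveal the arm before T3 and T4.

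Use the same collection method in both arms. Collection through HEFORA would be unsuitable: the control group does not use the platform, so the two satisfaction items common to both arms would be gathered differently by arm.

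Optionally, have the assessor record a guess of each participant's allocation at T4, so that the success of blinding can be reported, including for participants already past T2. A guess may also reflect observed recovery and should be read with that in mind.

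The cost is a small change in visit logistics for existing staff, with no new visit, measurement or change in sample size. Recruitment began in August 2024, so visits already completed gain no protection.
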